**Fig. 3 Fig3:**
[figure not shown]
Acupuncture points used in the study

Sterile stainless-steel disposable acupuncture needles (Huatuo, Suzhou, China; lengths and diameters 0.3 mm × 25 mm or 0.3 mm × 40 mm) will be used in this group. Among the points we choose, *Shouzhi-zhen* will be needled at an angle of 45–90° to the participant’s skin*,* while *Dingshen-zhen* and *Sishen-zhen* will be needled at an angle of 15–30° to the skin. The needles will be inserted at a depth of 5–30 mm. After that, the needles are stimulated manually to achieve the typical acupuncture sensation of *de qi*, which is characterized as soreness, numbness and heaviness. During every session, the acupuncture needles will be retained for 30 min and twirled every 10 min. JTN treatment will be discontinued if the patients suffer from any adverse events, and the acupuncture physicians can decide to terminate the trial.

#### Routine group

All participants in the control group will receive only MMT; they will not receive any treatment related to acupuncture after randomization for 10 weeks. During the study period, there will be five face to face visits and a diary will be collected. After the trial, all participants will have a chance to receive JTN treatment for 6 weeks as compensation.

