**Methods/design:**

This study is a parallel-arm, randomized controlled trial that aims to evaluate the efficacy and safety of acupuncture as adjunctive therapy for patients receiving MMT. A total of 140 eligible participants who range in age from 18 to 60 years and fulfil the Diagnostic and Statistical Manual of Mental Disorders, 5th edition (DSM-V), for opiate dependence will be enrolled into this study. All eligible participants will be randomly assigned to the acupuncture group or routine group in a 1:1 allocation ratio. Participants who are enrolled in the acupuncture group will receive MMT and JTN treatment for 30 min per session. Meanwhile, those who are assigned to the routine arm will receive MMT only. All 18 sessions of JTN treatment will be delivered over 6 weeks (3 per week) and followed by a 4-week follow-up period. The primary outcome measure will be the visual analogue scale (VAS) for drug craving and the daily consumption of methadone (DCOM). Secondary outcome measures will include the urine test for opioid use, the 36-item Short Form Survey (SF-36), the Beck Anxiety Inventory (BAI), the Beck Depression Inventory II (BDI-II) and Pittsburgh sleep quality index (PSQI). VAS, DCOM, BAI, BDI-II and the urine test for opioid use will be evaluated at baseline, the second week, the fourth week, the sixth week and the tenth week. SF-36 and PSQI will be assessed at baseline, the fourth week, the sixth week and the tenth week.

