### Intervention

The interventions will be performed by licensed acupuncturists with more than 3 years of experience in clinics. According to the traditional acupuncture theory and previous RCTs, the acupuncture study interventions were developed by a consensus of acupuncture experts. Before initiation of the study, the acupuncturists will obtain special training to gain total understanding of the treatment and receive a brochure that shows the acupuncture manipulation with detailed information. Subjects who are assigned to the acupuncture group will receive MMT and JTN treatment for 30 min per session. Meanwhile, those who are randomized to the routine group will receive MMT only. All 18 sessions of JTN treatment will be delivered over 6 weeks (3 per week) and followed by a 4-week follow-up period. The study schedule is shown in Fig. 2.

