### Outcome

#### Primary outcome

##### The daily consumption of methadone

Daily consumption of methadone from baseline to the 2nd, 4th, 6th and 10th weeks will be presented. One primary outcome measure will be the change in the daily consumption of methadone from baseline to the 6th week. The enrolled patients will go to the clinic to receive methadone every day, and the dosage will be strictly administered by the doctor, which will be recorded in the clinic computer system.

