### Safety

All participants will have some tests to check their body at screening and after 6 weeks of treatment. These tests will be relative to the heart, liver, kidney and other organs, including white blood cell count, haematocrit, haemoglobin, platelets, aspartate aminotransferase/alanine aminotransferase, blood urea nitrogen, creatinine, gamma-glutamyl transpeptidase, erythrocyte sedimentation rate and electrocardiogram.

Adverse events (AEs) are defined as any unexpected unfavourable signs, symptoms or feelings occurring in subjects during the entire period, whether or not associated with JTN treatment. Every AE will be fully recorded on the case report form (CRF), including all details of AEs. Serious AEs that threaten a participant’s life or result in hospitalization will be reported to the Research Ethics Committee concerned within 24 h. All the tests and AEs are recorded, with an aim to evaluate the safety of JTN.

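### Adverse events may be ascertained unequally: 20 to 23 scheduled study contacts in the acupuncture arm against 5 in the routine arm, with a diary mentioned only under the latter

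*Protocol article*

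**What the plan says.** The Intervention section sets the acupuncture schedule: "All 18 sessions of JTN treatment will be delivered over 6 weeks (3 per week) and followed by a 4-week follow-up period". The abstract's Methods/design paragraph gives the visit times for craving, methadone consumption, anxiety, depression and the urine test, which "will be evaluated at baseline, the second week, the fourth week, the sixth week and the tenth week". The Routine group section adds: "During the study period, there will be five face to face visits and a diary will be collected". The Acupuncture group section mentions no diary.

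The Safety section defines adverse events as those "occurring in subjects during the entire period, whether or not associated with JTN treatment" and requires each one to be entered on the case report form. It closes: "All the tests and AEs are recorded, with an aim to evaluate the safety of JTN". For laboratory tests and ECG it says: "All participants will have some tests to check their body at screening and after 6 weeks of treatment".

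Under Randomization, allocation and concealment, practitioners and patients know the allocation, while outcome assessors and data collectors do not. Under the daily consumption of methadone, the article adds: "The enrolled patients will go to the clinic to receive methadone every day, and the dosage will be strictly administered by the doctor".

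**The concern.** Counting events of any cause in both arms tells us about the safety of JTN mainly through comparison with the routine arm. Such a comparison is sound only if an event has a similar chance of being recorded in each arm. As written, acupuncture patients spend 18 half-hour sessions with an unblinded practitioner, and routine patients have no matching contact. A diary, if it is kept in the routine arm alone, is a second difference in how events come to light.

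Mild, subjective complaints are the most exposed, because whether they are recorded depends on who asks and how often. Blinded assessors at the common visits cannot remove events that reached the record through an unblinded session. At stake is whether a difference in event counts, or the absence of one, reflects JTN or the way the events were collected.

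**Working it through.** **Inputs from the Protocol article**
- JTN sessions: 18, at 3 per week for 6 weeks (Intervention).
- Assessment visits: baseline and weeks 2, 4, 6 and 10 (abstract and Outcome sections).
- Routine-group visits: five, plus a diary (Routine group).
- Daily methadone attendance, all enrolled patients (The daily consumption of methadone).
- Study length: 6 + 4 = 10 weeks. Arm size: 70.

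**Step 1. The plan's own counts.** 3 × 6 = 18 sessions, as stated. Baseline plus four later assessments makes 5 visits, which matches the five under Routine group. Those five visits are therefore the schedule common to both arms.

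**Step 2. Scheduled study contacts.**
- Weeks 2, 4 and 6 assessed on session days: 18 + 2 (baseline and week 10) = 20. Ratio 20/5 = 4.0.
- All assessments separate from sessions: 18 + 5 = 23. Ratio 23/5 = 4.6.

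**Step 3. Adding daily methadone attendance.** Ten weeks is about 70 days in each arm.
- Acupuncture: 70 + 20 = 90, or 70 + 23 = 93.
- Routine: 70 + 5 = 75.
- Ratio: 90/75 = 1.20, or 93/75 = 1.24.

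This lower ratio matters only if clinic staff pass adverse events to the trial. The article says that they record the dose and does not say that they collect events.

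**Step 4. What unequal capture could do.** The documents give no capture rates, so this step rests on assumptions: equal true risk in both arms, every event recorded in the acupuncture arm, and a share r of events recorded in the routine arm. The apparent risk ratio is then 1/r. With n = 70 per arm, p₁ = true risk, p₂ = r × p₁ and p̄ their mean, the chance of a spurious significant excess with acupuncture (two-sided 0.05) is

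Φ{ [p₁ − p₂ − 1.96 √(2p̄(1−p̄)/n)] / √([p₁(1−p₁) + p₂(1−p₂)]/n) }.

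Example: true risk 0.20 and r = 0.5 give p₂ = 0.10 and p̄ = 0.15. The two square roots are 0.0604 and 0.0598. Then (0.10 − 1.96 × 0.0604)/0.0598 = −0.31, and Φ(−0.31) is about 0.38.

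| r | Apparent risk ratio | True risk 10% | True risk 20% | True risk 30% |
|---|---|---|---|---|
| 0.3 | 3.3 | 39% | 70% | 89% |
| 0.5 | 2.0 | 20% | 38% | 57% |
| 0.8 | 1.25 | 6% | 9% | 12% |
| 1.0 | 1.0 | 2.5% | 2.5% | 2.5% |

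The last row is the reference: 2.5% is one tail of a two-sided 5% test. Because the arms are equal in size, the table also applies in mirror image. If a routine-only diary made capture better there, the same probabilities would describe a spurious excess in the routine arm. The table shows how sensitive a comparison could be. It does not estimate what will happen in this trial.

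**The case against.** A reader might infer that the routine arm is seen only five times, that adverse event rates therefore cannot be compared at all, and that the safety conclusion is uninterpretable. The documents do not support this, for several reasons.

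- **Daily clinic attendance.** Every patient in both arms meets a clinician daily for methadone. This is the strongest counterpoint and it stands as a limit on size. It does not remove the concern, because the 18 sessions remain an excess in one arm and the clinic is not said to collect events. Equally, the article does not say that acupuncturists ask about events. Its discontinuation provision suggests only that they are expected to notice them.
- **Symmetric tests.** Blood tests and ECG are scheduled identically for all participants, so that part of the safety data can be compared.
- **No stated test.** The Statistical analysis section names no between-arm comparison of adverse events, and events caused by needling can be described within the acupuncture arm alone. This stands. Still, an all-cause definition in a randomized trial with a safety aim invites a comparison, tested or not.
- **The diary.** The sentence that mentions the diary also mentions the five visits, and those apply to both arms. Placement under Routine group is thus weak evidence that the diary is control-only, and its content is not given. The schedule figure and the full protocol, neither of which is shown, may settle this.
- **The definition.** Adverse events are limited to unexpected ones, so known methadone effects or withdrawal symptoms may fall outside it. That narrows which events are affected.
- **Design.** Unequal contact is usual when an add-on treatment is compared open-label with usual care, and the Discussion acknowledges the open-label limitation. This explains the imbalance but does not protect the event counts from it.

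A reader might also infer that the bias must run against acupuncture. That is not supported either: a routine-only diary would work in the opposite direction, and the net effect is unknown.

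**Conclusion.** The concern holds in a limited form: adverse event ascertainment may differ between the arms. The contact counts are firm, at 20 to 23 scheduled study contacts against 5. They fall to a ratio of 1.20 to 1.24 if the methadone clinic also feeds events to the trial, which is not stated. The diary difference is possible but not established.

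The consequence for event counts depends on relative capture, on which the documents give nothing. Under the assumptions above it ranges from no effect (r = 1.0) to an apparent risk ratio of 3.3 (r = 0.3), and it could run either way. Laboratory and ECG findings are not touched. This is a design weakness that is worth correcting because it bears on a stated aim and costs little. It does not invalidate the safety evaluation.

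**What to change.** In the Safety section, state that adverse events are elicited with the same standard question, put by the blinded assessor, at the common visits (weeks 2, 4, 6 and 10) in both arms, and that any between-arm comparison of adverse events uses those data. Report events noted at JTN sessions in a separate table for the acupuncture arm only. Continue to report all serious adverse events in full, however they came to light. In the Routine group section, state that the diary is collected in the same form from both arms or from neither.

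The cost is one added question at existing visits, one added table and, if the diary is kept, the same form for the acupuncture arm. No extra visits or staff are needed. The price is that some events seen at sessions stay out of the between-arm comparison, though they remain reported. The change equalises the opportunity to report. It cannot remove differences in reporting that arise because patients know their allocation.

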### Outcome

#### Primary outcome

##### The daily consumption of methadone

Daily consumption of methadone from baseline to the 2nd, 4th, 6th and 10th weeks will be presented. One primary outcome measure will be the change in the daily consumption of methadone from baseline to the 6th week. The enrolled patients will go to the clinic to receive methadone every day, and the dosage will be strictly administered by the doctor, which will be recorded in the clinic computer system.

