## Background

According to the World Drug Report 2018, approximately 31 million people are affected by opioid use disorders through the world, which cause the greatest burden of severe disease and drug-related deaths worldwide [1]. In China, there are approximately 2.5 million people using illicit drugs, of which opioids and methamphetamines represent the majority [2].

Opioid dependence is a chronic psychiatric disorder. Discontinuation of the drug abruptly induces specific physiological and psychological changes called withdrawal, which is a temporary stage opposing intoxication towards re-establishment of the patient’s neuronal system. Withdrawal symptoms mainly include sweating, shaking and diarrhoea in the first few days, accompanied by dysphoria, depression, anxiety and insomnia, which may continue for several months [3, 4]. It is an unadaptable state associated with withdrawal symptoms and severe craving, which may lead to the high risk of relapse. The primary goal of treatment for opioid dependence usually focuses on achieving control of withdrawal symptoms and reducing cravings. Methadone has been used to treat withdrawal symptoms for several decades. Patients with opioid dependence have to receive MMT as replacement therapy for years or even their entire life. However, side effects of MMT still exist and have been reported to range widely, especially during the early weeks of methadone stabilization [5]. Patients often complain of insomnia and cravings during MMT, which contribute to the risk of relapse [6]. Therefore, it is necessary to seek a new treatment with efficacy and safety for patients receiving MMT.

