### Study subjects

Subjects will be recruited through advertisements at the Affiliated Brain Hospital of Guangzhou Medical University. All eligible individuals will be strictly assessed by an acupuncturist based on the criteria described below. Subjects are eligible to include if they (1) are male or female aged 18–60 years; (2) fulfil the criteria for the diagnosis of opioid dependence on the basis of the Diagnostic and Statistical Manual of Mental Disorders, 5th edition (DSM-V) [20]; (3) receive MMT for more than 30 days; (4) do not receive any kind of acupuncture therapy during the previous 3 months; and (5) are able to sign informed consent.

Subjects will be excluded if they have one or more of the following criteria: (1) serious heart, liver, lung or kidney disease; (2) venereal disease or AIDS; (3) the presence of severe digestive disease and athrepsia; (4) major psychosis; (5) the receipt other treatment that may affect the efficacy evaluation of the present intervention; (6) an infection, inflammation, scar or injury close to the site of the selected acupoints; or (7) are pregnant or planning to become pregnant.

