### Randomization, allocation and concealment

Eligible patients will be randomly assigned in an equal ratio to the acupuncture group or the routine group via a central randomization system. The randomization sequence will be generated in a block size of 4. Participants will be informed that they have an equal chance to be assigned to the acupuncture group or the routine group. After participants sign the informed consent form and complete baseline assessments, the researcher will assign them a randomization number and allocate the participants to each group. The allocation of participants will be performed by an independent researcher at the clinical site who was not involved in the assessment of outcomes. Due to the design of this study, practitioners and eligible subjects will know the allocated group, while the outcome assessors, data collectors and statisticians will be blinded to group allocations during the study.

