### Sample size calculation

The primary outcome measure for drug craving is VAS. Based on previous studies [5, 30], after 4 weeks of treatment, the VAS for drug craving score difference between the baseline and the endpoint in the sham acupuncture group should be approximately 20 ± 30, while the true acupuncture group should be approximately 37.5 ± 28. Type 1 error is assumed at 0.05, and type 2 error is assumed at 0.1. PASS11.0 software (CSS Statistical Software, Kaysville, UT, USA) has been used to determine the sample size, and the minimum sample size is 60 subjects for each group. Considering a dropout rate of 15%, a total of 140 subjects will be required with 1:1 allocation to each group (70 participants per group) for this study.

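### Mixed pre-baseline methadone dose courses add noise to the week-6 methadone change, and the stated unadjusted t test leaves that noise in; an adjusted analysis would recover some precision

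*Protocol article*

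**What the plan says.** **Endpoint.** Under the daily consumption of methadone, the Protocol article states: "One primary outcome measure will be the change in the daily consumption of methadone from baseline to the 6th week". The same section says that "the dosage will be strictly administered by the doctor, which will be recorded in the clinic computer system".

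**Entry.** The eligibility list under Study subjects has one condition on methadone treatment: "receive MMT for more than 30 days". It gives no upper limit and no condition on how the dose moved before baseline.

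**Allocation.** Randomisation is central and 1:1: "The randomization sequence will be generated in a block size of 4". No stratification factor is named. The comparator runs concurrently: "All participants in the control group will receive only MMT".

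**Analysis.** The Statistical analysis section compares group means with an independent-sample t test and explores time by treatment with a repeated-measures ANOVA. It mentions no covariate. The sample size is worked out on VAS craving alone.

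**The concern.** The Background describes methadone treatment that can last for years or for life, and it recognises an early stabilisation phase. The entry rule admits both a patient just past day 30 and one treated for years. If some patients are still having their dose changed at baseline, their week-6 dose will move with or without acupuncture, while a long-stable patient's dose will hardly move. A single baseline dose does not separate the two, because patients on the same dose may be rising, falling or flat.

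This extra spread goes straight into the standard error of the methadone comparison. The trial was sized on craving, so nothing in the article shows that 70 per arm leaves room for it. What is at stake is the chance of detecting a real methadone saving.

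**Working it through.** **1. The plan's own figure.** Inputs from Sample size calculation: VAS changes 20 ± 30 and 37.5 ± 28, type 1 error 0.05 (two-sided under Statistical analysis), type 2 error 0.1.

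- Pooled SD = √((30² + 28²)/2) = 29.02; difference = 17.5.
- The normal formula gives 58 per arm and the noncentral t gives 59. The article states 60.
- 59/0.85 = 69.4, so 70 per arm; 60/0.85 = 70.6, so 71. The article states 70.

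The figure reproduces, but it concerns craving. There is no counterpart for methadone.

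**2. Does mixed dose history bias the comparison?** Let a share *f* of patients be recently started, with mean change shifted by *D* within-group SDs. Neither value is in the documents, so *f* = 0.2 and 0.5 and *D* = 0.5, 1 and 2 were assumed. With no treatment effect, 70 per arm, an unadjusted t test and 20,000 simulated trials per scenario:

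- the rejection rate was 0.048 to 0.053;
- the mean between-arm difference was within ±0.003 SD of zero.

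The average within-arm change moved by 0.1 to 1.0 SD, but equally in both arms.

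**3. What does it cost in precision?** Variance inflation is 1 + *f*(1−*f*)*D*².

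- Mildest case: 1 + 0.16 × 0.25 = 1.04. A comparison with 90% power without the mixture would have 89%.
- Strongest case: 1 + 0.25 × 4 = 2.0. Power would be 63%.

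**4. An illustration in mg.** Assumed: stable patients change by 0 mg on average (SD 5); patients still being adjusted change by +10 mg (SD 15); their share is *q*.

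| *q* | Within groups: 25(1−*q*) + 225*q* | Between groups: 100*q*(1−*q*) | Total | SD unadjusted | SD with a stage factor |
|---|---|---|---|---|---|
| 0.2 | 20 + 45 = 65 | 16 | 81 | 9.0 | √65 = 8.1 |
| 0.3 | 17.5 + 67.5 = 85 | 21 | 106 | 10.3 | √85 = 9.2 |

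A factor removes only the between-group part: 16/81 or 21/106, about 20% in each case. Most of the inflation over the stable-patient variance of 25 comes from the assumed SD of 15, which no stratum or factor removes. At *q* = 0.3, 106/85 = 1.25, so the gain equals about 25% more patients for this outcome.

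**5. Chance imbalance.** At *q* = 0.3, the SE of the between-arm difference in share is √(2 × 0.3 × 0.7/70) = 0.077. A 10-point imbalance shifts the methadone difference by 0.10 × 10 = 1 mg. The SE of that difference is 10.3 × √(2/70) = 1.74 mg, so the shift is 1/1.74 = 0.57 SE.

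**6. Direction.** If half of the adjusted patients average +10 mg and half −10 mg, their overall mean change is 0, the same as in stable patients. The between-group part of a yes/no flag is then zero and it recovers nothing. A signed change keeps the direction.

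**The case against.** A reader might infer that methadone change in this trial largely reflects stage of treatment rather than acupuncture. The documents do not support that. Stage is fixed before randomisation, the control arm receives MMT over the same period, and step 2 shows no bias and an error rate near 5%. The inference could apply to change within one arm, but the trial compares arms.

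Three further objections stand in full:

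- Chance imbalance is not an additional harm. The t test's standard error already allows for it, and 1 mg is ordinary random error beside an SE of 1.74 mg.
- The Background's phrase "especially during the early weeks of methadone stabilization" is about side effects, not dose movement. The entry rule already excludes the first 30 days. That some patients are still being adjusted after that is plausible, but it is inferred.
- Every mg figure is assumed, and on those assumptions adjustment recovers only about a fifth of the variance.

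It can also be said that a mixed MMT population is a legitimate choice, and that covariates usually belong in an analysis plan, which is not shown. The first is right: the entry rule is not an error. The second stands in part. A full protocol or analysis plan may already adjust, but the article does name an unadjusted test for comparing means, and that statement can be improved.

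**Conclusion.** The point holds as a loss of precision, at low priority. The article combines an entry rule open to any dose history, no named stratum and an unadjusted test, for a primary outcome that was not sized. Differences in pre-baseline dose course can then widen the standard error of the methadone comparison. They do not bias it, and the documents do not support saying that they dominate it.

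The size cannot be fixed from the documents. Under the assumptions in step 4, adjustment removes about 20% of the variance. With a yes/no flag and mixed directions it removes less, down to none. Under the wider range in step 3 the loss runs from negligible to serious. What a signed covariate would recover depends on how well the recent dose trend predicts the next six weeks, which the documents do not show.

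**What to change.** For the week-6 methadone change, replace the unadjusted t test with a pre-specified linear model (ANCOVA) containing treatment arm, baseline dose, and the signed change in recorded dose over the 28 days before randomisation. Take the last from the clinic computer records. Entry requires more than 30 days of MMT, so the window should exist for every patient; that the records reach back before enrolment is an assumption to confirm. Specify the model for all patients, including those already randomised, before unblinding.

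A stratum on recent dose change for patients not yet randomised is optional. The covariate provides the gain in any case.

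The cost is a record look-up and slightly more analysis work. It adds no visits or patients and sets no rule on dose or eligibility.

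Suggested wording: *The change in daily methadone consumption from baseline to week 6 will be compared between arms by ANCOVA, adjusting for baseline dose and for the signed change in recorded dose over the 28 days before randomisation.*
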